## Methods/Design

### Study Design

Approval for the trial has been obtained from The University of Melbourne Human Research Ethics Committee (HREC 1136446). This study uses a wait-list control cluster randomised controlled trial to test the appropriateness, acceptability, feasibility, costs and effectiveness of the Thrive intervention program. The intervention program is being conducted with one FDC scheme based in a low socioeconomic area of Melbourne. A low socioeconomic area was selected because the prevalence of child mental health problems is higher in poorer areas [2].

Figure 1 summarises the study design and timelines. All FDC educators and field workers within the scheme are eligible to receive the intervention program. The clusters for randomisation will be the field workers (n = 5) who each supervise 10-15 educators. Randomisation will be conducted in accordance with ICH Guideline E9 [21] by [name], who is independent of the administration of the intervention.

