### Sample Size

Sample size is constrained to 35 per arm by the size of the organization hosting the trial. Nevertheless, under moderate assumptions, the study may have power to detect moderate size effects in its own right. Given the nature of the intervention and outcomes of comparable studies [27] such an effect is achievable and lies at the lower end of interest. Allowing for an ICC of 0.03 and average cluster size of 14 yields a design effect of 1.72 implying an effective sample size of 20 participants per arm. Assuming a correlation of 0.7 between pre- and post-test scores, the study will maintain 80% power to detect mean difference in change scores between groups of 0.7 standard deviations. Compared to trials of individual therapies, drop out in this study is expected to be restricted to normal worker turnover that is low and likely to be limited to the 12 month follow-up. It is acknowledged that precision in detecting between field worker differences and estimating ICCs will not be high. This is consistent with the exploratory nature of this study.

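### The ICC of 0.03, cluster size of 14 and design effect of 1.72 in the sample-size paragraph do not agree, and the protocol does not show which is wrong

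*Protocol article*

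**What the plan says.** The Sample Size section of the protocol article starts from a fixed number of participants: "Sample size is constrained to 35 per arm by the size of the organization hosting the trial". It then allows for clustering by field worker: "Allowing for an ICC of 0.03 and average cluster size of 14 yields a design effect of 1.72". From that design effect it shrinks the 35 per arm to an effective 20. The last step is the power statement: "Assuming a correlation of 0.7 between pre- and post-test scores", the trial is said to keep 80% power for a between-group difference in change scores of 0.7 SD.

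The Study Design section describes the clusters: "The clusters for randomisation will be the field workers (n = 5) who each supervise 10-15 educators". With about 70 participants in all, 70/5 = 14, so the stated average cluster size fits the rest of the document.

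The paragraph gives no other formula, no allowance for varying cluster size, no numerical dropout inflation and no significance level.

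**The concern.** The two inputs and the result stand in one sentence, and the result is not what the usual formula gives. The design effect turns 35 participants per arm into an effective 20, and the 0.7 SD is worked out from that 20, so the whole power statement depends on it.

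What is at stake is whether the justification can be reproduced. As printed, a reader cannot tell whether the trial was planned on an ICC of 0.03 or on one nearly twice as large. Nor can the reader tell whether the quoted effective sample size and detectable difference belong to the stated assumptions.

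**Working it through.** **Inputs.** From the Sample Size section: ICC 0.03; average cluster size m = 14; design effect 1.72; 35 per arm; effective n of 20 per arm; pre-post correlation 0.7; 80% power at 0.7 SD. From the Study Design section: 5 clusters of 10 to 15 educators. Assumed here, because the document gives no value: two-sided alpha of 0.05.

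**1. Do the later figures follow from 1.72?** Yes.
- Effective n per arm = 35/1.72 = 20.3, printed as 20.
- Change-score variance in raw-score SD units = 2(1 - 0.7) = 0.6, so the SD is 0.775.
- Detectable difference at n = 20, normal approximation: (1.960 + 0.842) x 0.775 x sqrt(2/20) = 0.69 SD. With the t distribution it is 0.70 SD.
- Power at 0.7 SD with n = 20: 81.5% (normal) or 79.5% (t). With n = 20.3 the t-based power is 80.2%.

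So 1.72 was carried through the calculation. It is not merely a misprint of a design effect that was correct in the working.

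**2. Does 1.72 follow from its own inputs?** No.
- Design effect = 1 + (m - 1) x ICC = 1 + 13 x 0.03 = 1.39.

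**3. Does a variant formula reach 1.72 at ICC 0.03?** None that fits the described clusters.
- Using m in place of m - 1: 1 + 14 x 0.03 = 1.42.
- Cluster sizes from 10 to 15: 1 + 9 x 0.03 = 1.27 up to 1 + 14 x 0.03 = 1.42.
- Unequal clusters, 1 + ((1 + CV^2) x 14 - 1) x ICC: 1.41 at CV 0.2, 1.43 at CV 0.3 and 1.50 at CV 0.5. Reaching 1.72 takes a CV of about 0.89, whereas five clusters of 10 to 15 can have a CV of only about 0.2.

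**4. What would give 1.72?**
- With m = 14: ICC = 0.72/13 = 0.055. As a check, 1 + 13 x 0.055 = 1.715.
- With ICC = 0.03: m = 0.72/0.03 + 1 = 25, outside the stated 10 to 15.
- Over the whole stated range of cluster sizes, the ICC would have to lie between 0.72/14 = 0.051 (m = 15) and 0.72/9 = 0.080 (m = 10). No permitted cluster size is compatible with 0.03.

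**5. What each reading implies, on the plan's own individual-level method.**

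| | (a) ICC 0.03 and m = 14 stand | (b) 1.72 stands |
|---|---|---|
| ICC | 0.03 | about 0.055 |
| Design effect | 1.39 | 1.72 |
| Effective n per arm | 35/1.39 = 25.2 | 35/1.72 = 20.3 (printed as 20) |
| Detectable difference at 80% power (normal / t) | 0.61 / 0.62 SD | 0.69 / 0.70 SD (n = 20) |
| Power at 0.7 SD (normal / t) | 89% / 88% | 81.5% / 79.5% (n = 20) |

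**The case against.** The best defence is that little hangs on the slip. The sample is capped by the size of the host organisation, so the design effect set no recruitment target. The study is described as exploratory, and its power claim is worded cautiously. Under reading (a) the printed figures err on the safe side; under reading (b) the power statement is unchanged. All of this stands and limits the severity. It does not make the sentence correct: the exploratory label excuses imprecise estimation of the ICC, not inputs and a result that disagree. Nor is this detail that an article leaves to a fuller document, because the inputs and the result are all printed.

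Three stronger readings are tempting, and the document supports none of them.

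- *The effective sample size and the 0.7 SD are wrong.* A reader might infer this from 1.39 alone. But both figures follow from 1.72. If the ICC is the misprint, then 1.72, 20 and 0.7 SD all stand and a single number changes.
- *The error overstates the trial's power.* It does so under neither reading: the printed power is too low under (a) and unchanged under (b).
- *The trial really has 88% power.* That figure comes from treating the participants, after deflation by the design effect, as independent individuals. The method ignores that only five clusters are randomised, a separate matter that this check does not cover.

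It would also go too far to say that 0.03 is offered as an estimate for other studies. It is a planning assumption. The Data Analysis section plans to estimate the ICC from the trial's own data, and the Sample Size section concedes that this estimate will not be precise.

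**Conclusion.** The point holds as an internal inconsistency. An ICC of 0.03 with 14 per cluster gives a design effect of 1.39, not 1.72, and no standard variant compatible with 10 to 15 educators per field worker closes the gap. The document does not show which number is wrong.

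The size depends on the reading. Under (a), the effective n is understated by about 5 per arm (25.2 against 20) and the detectable difference is overstated by about 0.08 SD (0.62 against 0.70, t-based). Under (b), the printed ICC is little more than half of the one used (0.03/0.055 = 0.55). The power and detectable-difference figures assume a two-sided alpha of 0.05 and 0.7 SD expressed in raw-score units, which is the reading that reproduces the printed result. The design-effect mismatch itself needs neither assumption.

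Severity is moderate: a figure that the power statement relies on cannot be right as printed with its inputs, but design, recruitment and conduct are unaffected.

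**What to change.** Go back to the original calculation, establish which number is wrong, and restate the Sample Size paragraph so that its figures agree. There are two candidate corrections:

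- **(a)** Keep the ICC of 0.03 and cluster size of 14. Restate the design effect as 1.39, the effective sample size as about 25 per arm, and the detectable difference at 80% power as about 0.61-0.62 SD (about 88% power at 0.7 SD).
- **(b)** Keep the design effect of 1.72, the 20 per arm and the 0.7 SD, and correct the ICC to about 0.055.

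In either case, state the significance level and name the design-effect formula. Say also that the power figure comes from an individual-level approximation that takes no account of there being only five clusters, so that under (a) the 88% is not read as the trial's actual power.

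The cost is one corrected paragraph, with no change to recruitment or conduct.

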### Development of Thrive

The initial stages of the project comprised telephone interviews and focus groups with FDC educators. Their responses guided the development of the intervention program. Telephone interviews were completed with 50 educators to help gain insight into their knowledge and confidence in promoting children's social and emotional wellbeing. This information provided useful insights and allowed educators to be categorised into different 'stages of change' [20] around their willingness to promote children's social and emotional wellbeing. The Stages of Change model has been widely used in health promotion programs and describes the stages an individual or organisation moves through from before they contemplate changing, to contemplating change, taking action, maintaining the new practice and also relapsing. These categories were used to assemble focus groups bringing together educators who were at similar stages of willingness to actively promote children's social and emotional wellbeing in their FDC practice. Four focus groups were conducted (three with educators in the action/maintenance phase, and one with fieldworkers) and five individual interviews with educators in the 'relapse', 'pre-contemplation' and 'preparation' stages. In addition, system perspectives were gained through six key informant interviews with representatives from peak bodies, training organisations, scheme sponsor management and government.

The Thrive program includes several activities for field workers and FDC educators. These activities include workshops for field workers (N = 4) and FDC educators (N = 3), activity exchanges with other educators and focused discussion on social and emotional wellbeing during field worker visits. The intervention group will also receive resources associated with the workshops on promoting children's social and emotional wellbeing. A cluster randomised controlled trial design is being used because the effectiveness of some of the intervention activities (i.e. activity exchange and field worker visits) is dependent on the field worker.

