### Data Analysis

Primary analyses will be undertaken on an intent-to-treat basis, including all participants randomized regardless of the extent of participation in the intervention or withdrawal from the study. Mixed-model repeated measures analyses will be used because of the ability of this approach accommodate clustering effects, appropriately model the relationship between measures over time and to include participants with missing data [25,26]. Planned contrasts will test hypotheses address the effectiveness of the program compared to control at post-test, and six months and 12 months follow-up. Exploratory analyses of clustering (i.e. field worker) effects will be undertaken including estimation of the intra class correlation (ICC). Of particular interest are the effects at post-test after field workers have delivered the intervention. While the number of field workers is small, it is hoped to enhance precision of estimation by using the pre-, post-intervention data from control participants from the phase of the trial where they receive the intervention.

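### The stated 80% power for 0.7 SD counts effective educators as independent; with five randomised field workers, a test that holds its 5% level has about 49–58% power

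*Protocol article*

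**What the plan says.** Under Study Design, the protocol article sets the unit of randomisation: "The clusters for randomisation will be the field workers (n = 5) who each supervise 10-15 educators". Under Development of Thrive it explains the cluster design by noting that "the effectiveness of some of the intervention activities (i.e. activity exchange and field worker visits) is dependent on the field worker".

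The Sample Size section starts from a fixed number: "Sample size is constrained to 35 per arm by the size of the organization hosting the trial". It allows for clustering through a design effect: "Allowing for an ICC of 0.03 and average cluster size of 14 yields a design effect of 1.72 implying an effective sample size of 20" per arm. It then adds a pre-post correlation ("Assuming a correlation of 0.7 between pre- and post-test scores") and concludes that "the study will maintain 80% power to detect mean difference in change scores between groups of 0.7 standard deviations".

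The same section concedes low precision for differences between field workers and for the ICC, and links this to the exploratory aim. It makes no such concession for the comparison of the two arms. Under Data Analysis: "Mixed-model repeated measures analyses will be used because of the ability of this approach accommodate clustering effects". No method for the degrees of freedom is given there.

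**The concern.** Dividing by a design effect enlarges the variance of the arm difference to allow for clustering. It does not allow for the fact that this variance must itself be estimated, and that its between-cluster part can be learned only from the five field workers. With two arms, five clusters leave 3 degrees of freedom, and the two-sided 5% critical value rises from 2.02 (38 degrees of freedom) to 3.18. A power figure that skips this step is too high.

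The Sample Size section places the target effect at the lower end of what is of interest, and Data Analysis plans contrasts of effectiveness at several time points. A reader who trusts the 80% would take a non-significant result as fair evidence against a 0.7 SD effect, when a valid test would have only about an even chance of finding one.

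**Working it through.** **Inputs.** From Sample Size: 35 per arm, ICC 0.03, average cluster size 14, design effect (DE) 1.72, effective n 20 per arm, pre-post correlation 0.7, difference 0.7 SD. From Study Design: five clusters. Assumed: two-sided alpha of 0.05, a split of two against three clusters of 14 (28 v 42 educators) where a layout is needed, and no dropout.

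**1. Reproduce the plan's figure.**
- Variance of a change score = 2(1 − 0.7) = 0.60; SD = 0.775.
- Effective n = 35/1.72 = 20.3, taken as 20.
- SE = 0.775 × √(2/20) = 0.245; noncentrality = 0.7/0.245 = 2.86.
- Two-sample t-test with 38 df: power 79.5% (normal approximation 81.5%).

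This matches the stated 80%, so the calculation treats 20 v 20 educators as independent.

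**2. Check the design effect.** 1 + (14 − 1) × 0.03 = 1.39, not 1.72. The stated 1.72 would need an ICC of 0.72/13 = 0.055, or a cluster size of 1 + 0.72/0.03 = 25. This is a separate slip, but it decides which figure applies below, so both values are carried.

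**3. Same inputs, 3 df.** Power comes from the noncentral t with 3 df and critical value 3.182. For two against three clusters, SE = √[0.60 × DE/14 × (1/2 + 1/3)]. For equal arms, SE = √(0.60 × 2/n), with n the effective number per arm. The noncentrality that gives 80% power at 3 df is 4.256, so the detectable difference is 4.256 × SE.

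| Layout | DE | SE | Noncentrality | Power at 0.7 SD | 80%-power difference |
|---|---|---|---|---|---|
| 20 effective per arm | 1.72 | 0.245 | 2.86 | 49.7% | 1.04 SD |
| 2 v 3 clusters of 14 | 1.72 | 0.248 | 2.82 | 48.9% | 1.05 SD |
| 2 v 3 clusters of 14 | 1.39 | 0.223 | 3.14 | 56.8% | 0.95 SD |
| 35 per arm | 1.39 | 0.218 | 3.21 | 58.3% | 0.93 SD |

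**4. What the mixed model would do.** Simulation of 400,000 trials per setting: 2 v 3 clusters of 14, change variance 0.60, REML with a random intercept for field worker.

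| Test of the arm contrast | ICC | Type I error | Rejection at 0.7 SD |
|---|---|---|---|
| z, uncorrected | 0.03 | 6.7% | 83.8% |
| z, uncorrected | 0.055 | 8.4% | 78.0% |
| t on cluster means, 3 df | 0.03 | 5.0% | 57% |
| t on cluster means, 3 df | 0.055 | 5.0% | 49% |
| Satterthwaite-type (3 df, or 68 if the cluster variance is estimated as zero) | 0.03 | 4.5% | 59% |
| Satterthwaite-type (as above) | 0.055 | 5.2% | 51% |

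Residual df (68) in place of z gives 6.3% and 7.9% type I error. The uncorrected test therefore comes near 80% only by exceeding its nominal level. Tests that hold the level, or nearly so, have 49–59% power.

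**5. Sensitivity to the assumed alpha.** At a one-sided 5% level, 3-df power is 70% with 20 effective per arm and 78% with DE 1.39 and 35 per arm. Neither reaches 80%.

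**The case against.** The best defence is that the article is candid about its limits. The size is fixed by the host organisation, the study is called exploratory, the text says only that it may have power, and Data Analysis admits that field workers are few. The 80% did not determine the sample size. All of this stands and lowers the stakes, but it does not make the figure right. The hedge is followed by an unqualified 80%, and the caveat on precision is confined to field-worker differences and the ICC. Using the control group's later intervention phase might add precision, but it forms no part of the power statement and adds no clusters.

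Three stronger readings are tempting, and the article does not support them.
- A reader might infer that the trial suffers both low power and inflated false positives. These belong to different tests: the uncorrected one keeps roughly the stated rejection rate and exceeds 5%, while the corrected one holds about 5% and loses power.
- A reader might infer that the planned p-values are anti-conservative. The article names neither z, residual nor any other degrees of freedom, and a condensed article may leave that to a fuller document. The inflation is conditional, and moderate at the ICCs the plan states or implies.
- A reader might infer that field worker is left out of the primary model, or that raw change will be analysed. The mixed model is chosen precisely because it can handle clustering; what is exploratory is the separate study of field-worker effects and the ICC. Change scores appear only in the power sentence.

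**Conclusion.** The concern holds for the power statement. The 80% for 0.7 SD is correct only if effective educators are independent units, which randomising five field workers rules out. With 3 degrees of freedom the figure is about 49–50% at the stated design effect of 1.72, or about 57–58% once the design effect is corrected to 1.39. Correcting that slip alone does not restore 80%. These results rest on a two-sided 5% level, the plan's own correlation and ICC, balanced clusters and no dropout.

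On type I error the conclusion is conditional: about 6.7% (ICC 0.03) to 8.4% (ICC 0.055) if the planned model is tested with z, and close to 5% if cluster-level degrees of freedom are used.

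**What to change.** **Sample Size.** Replace the 80%/0.7 SD claim with a 3-df statement, and say which design effect and alpha it uses. With 1.39: about 57% power at 0.7 SD, or a detectable difference of about 0.95 SD for two against three clusters of 14. With 1.72: about 49% and 1.05 SD, with the ICC or cluster size changed so that 1.72 follows from it. Add that the result will be read as an estimate with its confidence interval, so that a non-significant contrast is not taken as evidence against a 0.7 SD effect.

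**Data Analysis.** State that the arm contrast from the mixed model already planned uses cluster-level degrees of freedom, either through a small-sample correction or through a 3-df t-test on five baseline-adjusted cluster means.

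**Cost.** Wording in two paragraphs and one model option. The stated power becomes less favourable, and intervals are wider than with z or residual degrees of freedom. No extra participants or data are needed.

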## Discussion

Childhood mental health problems are highly prevalent. The FDC system is an ideal sector to promote child mental health. This project aims to conduct an exploratory wait-list control cluster trial of a mental health promotion intervention for children in FDC. It will explore the feasibility, costs and effectiveness of an intervention that builds the capacity of FDC settings to promote children's mental health. This initiative is the first internationally, and is essential to build an evidence base of interventions in this extremely policy-timely setting.

Rarely is solution-oriented intervention research designed and conducted with a rigorous methodology in a community of extreme disadvantage. One of the motivations for this research is that it might serve as a model for the FDC and childcare sectors. With a strong evidence base, the THRIVE program may be implemented widely within the sector nationally, thus addressing a key area of children's health inequalities - mental health. Initial results of this study will become available in 2012.

## Abbreviations

FDC: Family Day Care; FCCERS-R: Family Child Care Environment Rating Scale Revised Edition; CIS: Caregiver Interaction Scale; ICC: Interclass Correlation
